#### *Time To First Variceal Bleed*

Time to first variceal bleed will be compared between treatment groups using standard survival analysis methods. Kaplan-Meier survival curves will be constructed for visual presentation of time-to-event comparisons. Cox proportional hazard models will be fitted to obtain adjusted treatment effects which will be expressed as hazard ratios with 95% confidence intervals.

#### *Mortality at one year*

For all-cause mortality, the number and percentage of participants who have died within one year of randomisation will be reported by treatment group. An adjusted risk ratio and 95% confidence interval will be estimated from a log-binomial regression model. Risk difference will also be reported. Liver-related mortality and cardiovascular mortality will be analysed in the same way.

#### *Transplant free survival at one year*

This will be analysed and reported in the same way as all-cause mortality.

#### *Adverse events relating to treatment*

These events (as listed in section 4.4) will be analysed and reported in the same way as all-cause mortality.

#### *Other complications of cirrhosis*

These events (as listed in section 4.4) will be analysed and reported in the same way as all-cause mortality.

#### *EQ-5D-5L*

Both the EQ-5D-5L score and the health status score will be reported using means and standard deviations. The scores will be compared separately between treatment groups with adjusted mean differences and 95% confidence intervals estimated using linear regression models. Changes in both scores from baseline will also be separately modelled.

A template for reporting the secondary outcomes is given in the final report template.

## **9.7. Analysis methods – exploratory outcomes and analyses**

Any data that do not form a pre-specified outcome will be presented using simple summary statistics by intervention group (i.e. numbers and percentages for binary data and means (or medians) and standard deviations (or inter-quartile ranges) for continuous normal (or non-normal) data).

Outcomes related to treatment will be presented for the subset of participants that crossed over during the trial. The results will be compared alongside outcomes for participants that did not cross over.

### **9.8. Safety data**

The number and percentage of participants experiencing any adverse events, serious adverse events (SAEs) and suspected unexpected serious adverse reactions (SUSARs) will be presented by intervention group. A table for listing further details on the SAEs is provided in the final template report. Where applicable, this includes details on the dosage participants were on when the SAE occurred for those participants receiving carvedilol.

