## 4.7. Sample size

The sample size calculation has been based on published data from both a Cochrane meta-analysis of variceal banding versus beta-blockers and data from the first UK randomised trial of carvedilol published in this disease area. The Cochrane meta-analysis reported an overall 1-year variceal bleeding rate of 12% in the variceal banding ligation group. The 1-year bleeding rate was chosen for the primary outcome as Kaplan-Meier curves suggest that the majority of variceal bleeding occurs in the first year after treatment. In order to detect a 33% proportional difference in variceal bleeding rates (i.e. from 12% to 8%, a 4% absolute difference) between groups using a 2-sided test for comparison of proportions with a 1:1 allocation ratio, 90% power and a type I error rate of 5% (i.e.  $\alpha=0.05$ ), requires 2362 participants (1181 per group). Assuming and adjusting for a 10% attrition/loss to follow-up rate (based on the similar patient population studied), which is thus a conservative estimate due to our shorter duration of follow-up), increases the required sample size to 2630 participants in total (1315 per group).

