#### **Secondary outcome measures**

##### *Time to first variceal bleed*

Variceal bleeding events are identified as adverse events on the 6 month and 12 month follow-up forms. If a participant has at least one episode of variceal bleeding (including banding-related bleeding) indicated on either of these follow-up forms then they have “experienced variceal bleeding”. Participants which do not fulfil this criteria for experiencing variceal bleeding will be termed “free from variceal bleeding”.

If a participant is termed as having “experienced variceal bleeding” then their time until bleeding will be defined as the number of days from the date of randomisation till the date of onset for the first variceal bleed occurring.

Participants who are termed as “free from variceal bleeding” and who were last known to be

bleeding-free prior to the 12-month follow-up time-point will be censored in the analysis. The time to censoring will be the number of days from the date of randomisation to the date last known to be free from variceal bleeding. This will be determined by the completion date of the most recent trial form received e.g. date of completion on the 12-month follow-up form. If the last known date in the trial is equal to the date of randomisation then the participant will be censored at day 1.

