### **9.10. Sensitivity analyses**

Sensitivity analyses will be limited to the primary outcome and will consist of:

- An analysis is performed the same way as the primary analysis described in section 9.5 but now limited to the population that adhered to the allocated intervention as described in section 5.4.
- An analysis is performed to assess the effect of missing responses, in particular, the risk of bias they present. In the primary analysis described in section 9.5, all those recruited who have not reported variceal bleeding within 12 months are assumed to not have experienced the event. Here it is assumed that those who did not report variceal bleeding but have withdrawn, are lost to follow-up or have died within the 12-month follow-up period are missing the primary outcome response. Note that participants who are still actively in the trial at 12-months (are not withdrawn or lost to follow-up) but do not return the 12-month follow-up form will not be assumed missing.

Making these assumptions, firstly, an analysis is performed restricted to the population which has non-missing responses. Secondly, it is assumed that those with a missing response did not have variceal bleeding - the rationale being that the trial team would be

aware if bleeding had occurred due to the seriousness of the event and subsequent completion of an SAE form. Thirdly, the missing responses are assumed to be missing at random and are imputed via multiple imputation. In these three scenarios, the subsequent analysis performed is conducted in the same fashion as the primary analysis described in section 9.5.

- An analysis is performed on the primary analysis population in the same way as described in section 9.5 but with no covariate adjustment.

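### The any-AE and any-SAE totals in SAP 9.8 include variceal bleeds, so a benefit on the primary outcome can offset an excess of other events that have no comparison of their own

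*SAP*

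**What the plan says.** Section 9.8 of the SAP defines the overall safety summary: "The number and percentage of participants experiencing any adverse events, serious adverse events (SAEs", followed by SUSARs, each by intervention group. It excludes no event type and has no row without the primary outcome. For SAEs it adds a table listing further details, which sits in a separate report template (Appendix D).

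Two other sections place variceal bleeding inside these counts. Section 9.4, under time to first variceal bleed, states: "Variceal bleeding events are identified as adverse events on the 6 month and 12 month follow-up forms". Section 9.10, explaining why a missing response may be taken as no bleed, says that the trial team would be "aware if bleeding had occurred due to the seriousness of the event and subsequent completion of an SAE form".

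Section 9.6 plans separate between-group comparisons (adjusted risk ratio, 95% confidence interval and risk difference) for:

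- all-cause, liver-related and cardiovascular mortality;
- transplant-free survival;
- the four treatment-related events named in 4.4 (dysphagia, symptomatic hypotension, dyspnoea, gastrointestinal upset);
- the five other complications of cirrhosis named in 4.4.

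**The concern.** An overall row for any SAE is normally read as a measure of harm. Here it also carries the efficacy result: if one arm bleeds less, its any-SAE percentage falls for that reason alone. A real excess of other serious events in that arm would push the percentage back up, and the two movements can cancel. The same applies to the any-AE row.

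What is at stake is narrow but real. For an AE or SAE outside the categories compared in 9.6, section 9.8 specifies only the totals and a listing. A listing gives detail on individual events but does not set the arms side by side. The issue also reaches monitoring. Section 4.9 says that the SAP's methods will be followed in the DMC report where possible, and section 4.10 makes the absence of prohibitive safety concerns a condition for leaving the pilot phase.

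**Working it through.** **Inputs from the SAP.** Section 4.7 gives the bleeding risks ("i.e. from 12% to 8%, a 4% absolute difference"), a two-sided comparison of proportions with 1:1 allocation, 90% power, a 5% type I error rate, 1181 per group before attrition and 1315 per group after it.

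**Input not in the SAP.** The rate of SAEs other than variceal bleeding, q, is not given. I assume values from 5% to 60% in the arm with more bleeds.

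**Step 1: reproduce the plan's figure.** With the pooled-variance formula and mean risk 0.10:

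n = [1.960 × √(2 × 0.10 × 0.90) + 1.282 × √(0.12 × 0.88 + 0.08 × 0.92)]² / 0.04²

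This gives just over 1180, so 1181 per group and 2362 in total, as stated. Dividing 2362 by 0.90 gives 2625; the plan's 2630 is slightly higher. The sample size is not affected by this point.

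**Step 2: bleeds entering the SAE count.** If each bleed yields an SAE form, then per 1315 participants:

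- 0.12 × 1315 = about 158 in one arm;
- 0.08 × 1315 = about 105 in the other;
- the difference is about 53 participants, or 4 points.

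**Step 3: no overlap.** If bleeds and other SAEs fall in different participants, any SAE = q + bleeding risk. The rows are equal when other SAEs are 4 points higher in the arm with fewer bleeds. Example: 20% + 12% = 32% and 24% + 8% = 32%.

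**Step 4: independence.** Any SAE = 1 − (1 − q)(1 − bleeding risk).

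- With q = 20% in both arms: 1 − 0.80 × 0.88 = 29.6% against 1 − 0.80 × 0.92 = 26.4%. There is a gap with no difference in other SAEs.
- The rows are equal when q in the arm with fewer bleeds is 1 − (0.88/0.92)(1 − q). The hidden excess is therefore (1 − q) × 0.04/0.92.

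| Other SAEs, arm with more bleeds (assumed) | Other SAEs, arm with fewer bleeds | Hidden excess (points) | Any SAE, both arms |
|---|---|---|---|
| 5% | 9.1% | 4.1 | 16.4% |
| 10% | 13.9% | 3.9 | 20.8% |
| 20% | 23.5% | 3.5 | 29.6% |
| 30% | 33.0% | 3.0 | 38.4% |
| 40% | 42.6% | 2.6 | 47.2% |
| 60% | 61.7% | 1.7 | 64.8% |

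At the lowest rate the excess slightly passes 4 points, because some of the extra events fall in bleeders who are already counted.

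**Step 5: heavier overlap.** If a share s of bleeders in each arm also has another SAE, any SAE = q + bleeding risk × (1 − s), and the hidden excess is 4 × (1 − s) points:

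- s = 25%: 3 points (about 39 participants);
- s = 50%: 2 points (about 26);
- s = 75%: 1 point (about 13).

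**Step 6: what a separate row would show.** With 1315 per group and a two-sided 5% test, other SAEs of 20% against 24% would be detected with about 70% power, and 20% against 23.5% with about 58%. Section 9.8 plans no test, so these figures only indicate how visible the excess would be once shown apart.

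**The case against.** The strongest case on the other side has five parts.

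- **Most foreseeable harms are already compared.** Section 9.6 covers deaths, transplant-free survival, the four named treatment-related events and the cirrhosis complications, and bleeding in the any-SAE row cannot mask those comparisons. This stands and limits the point to events outside those lists. Section 9.7 also promises simple summaries by group for data that are not pre-specified outcomes, but it does not commit to an AE or SAE row without bleeds.
- **The template is not at hand.** It may already break SAEs down by arm and category. That is possible, but 9.8 itself describes only a listing.
- **Section 9.8 is descriptive.** It has no test or decision rule, and reporting all AEs and SAEs is ordinary complete reporting. This stands, which is why the totals should remain.
- **The SAE premise is indirect.** Section 9.10 gives a rationale, not a reporting rule, and the protocol's SAE rules are not shown. This stands for the SAE row. For the AE row, section 9.4 is explicit.
- **Overlap reduces the effect.** Section 2 reports 15% inpatient mortality and up to 40% one-year mortality in patients admitted with variceal bleeding, so other serious events in bleeders are plausible. This stands, and the working shows the range.

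A reader might infer that the bleeding benefit can hide an exactly equal excess of harm, or that harms are hidden throughout the report. The documents support neither. Exact equality needs bleeds and other SAEs never to occur in the same participant, and the comparisons in 9.6 are unaffected.

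**Conclusion.** The point holds in limited form. By the SAP's own text the primary outcome sits inside the any-AE total and is expected to sit inside the any-SAE total, and no row separates it.

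At the planned effect, the any-SAE row can absorb an excess of other SAEs of 4 points with no overlap, about 1.7 to 4.1 points under independence across the assumed rates, and about 1 point with 75% overlap. These sizes rest on the planning risks, on each bleed producing an SAE form, and on assumed rates of other SAEs. If the true bleeding difference is smaller, the excess that can be absorbed is smaller too.

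The exposure is confined to AEs and SAEs outside the categories compared in 9.6. The primary analysis and sample size are untouched.

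A reader might go further and want every outcome event removed, with the safety conclusion resting on what is left. The documents do not support that. Survival and complications of cirrhosis are studied as treatment effects (section 3), and the bleeding definition in 9.4 includes banding-related bleeding, a possible procedural harm. Removing all of these would create new masking.

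**What to change.** In section 9.8, keep the totals and add beside them, by arm:

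1. the number and percentage of participants with any AE other than variceal bleeding;
2. the number and percentage with any SAE other than variceal bleeding;
3. banding-related bleeding on its own row, as a possible procedural harm;
4. SAEs by CTCAE category, which section 9.4 shows is already on the SAE form.

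Do not exclude deaths or complications of cirrhosis from the new rows. State that the new rows are to be read together with the totals, not in place of them. Use the same rows in the DMC report where possible.

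The cost is a slightly longer table. Apart from separating banding-related bleeding, which depends on how the follow-up forms record it, the rows use information that the SAP already describes as collected.

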### **9.9. Planned subgroup analyses**

Interpretation of subgroup analysis will be treated with caution (output will be treated as exploratory rather than definitive). Analysis will be limited to the primary outcome only and the subgroups will be formed around the same variables used in the minimisation algorithm. Tests for statistical heterogeneity will be performed prior to any examination of effect estimates within subgroups. The effects of these subgroups will be examined by including a treatment group by subgroups interaction parameter in the final regression model. P-values for the interactions will be presented for these and interpreted with appropriate caution due to the reduced power. Analysis of primary outcome will be performed and reported within each subgroup in the same fashion as the primary analysis as described in section 9.5. A template for reporting this analyses is given in the final report template.

### **9.10. Sensitivity analyses**

Sensitivity analyses will be limited to the primary outcome and will consist of:

- An analysis is performed the same way as the primary analysis described in section 9.5 but now limited to the population that adhered to the allocated intervention as described in section 5.4.
- An analysis is performed to assess the effect of missing responses, in particular, the risk of bias they present. In the primary analysis described in section 9.5, all those recruited who have not reported variceal bleeding within 12 months are assumed to not have experienced the event. Here it is assumed that those who did not report variceal bleeding but have withdrawn, are lost to follow-up or have died within the 12-month follow-up period are missing the primary outcome response. Note that participants who are still actively in the trial at 12-months (are not withdrawn or lost to follow-up) but do not return the 12-month follow-up form will not be assumed missing.

Making these assumptions, firstly, an analysis is performed restricted to the population which has non-missing responses. Secondly, it is assumed that those with a missing response did not have variceal bleeding - the rationale being that the trial team would be

aware if bleeding had occurred due to the seriousness of the event and subsequent completion of an SAE form. Thirdly, the missing responses are assumed to be missing at random and are imputed via multiple imputation. In these three scenarios, the subsequent analysis performed is conducted in the same fashion as the primary analysis described in section 9.5.

- An analysis is performed on the primary analysis population in the same way as described in section 9.5 but with no covariate adjustment.

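### Two of the three missing-data scenarios in SAP 9.10 ignore the known bleed-free time of early leavers and treat bleed-free deaths as lost data, which modestly overstates the 1-year bleeding risk

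*SAP*

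**What the plan says.** The primary analysis counts a participant as bleed-free unless there is evidence of a bleed (SAP 9.3 and 9.5), so it has no missing outcomes. Section 9.10 relaxes this for the same outcome: "those who did not report variceal bleeding but have withdrawn, are lost to follow-up or have died within the 12-month follow-up period are missing". Three scenarios follow:

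1. Complete case: "an analysis is performed restricted to the population which has non-missing responses".
2. Missing taken as no bleed, which is the primary assumption again.
3. Multiple imputation under missing at random. No imputation model is given, follow-up time is not mentioned, and deaths are not separated from losses.

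For time to first bleed, section 9.4 already derives an exit date for bleed-free participants: "The time to censoring will be the number of days from the date of randomisation to the date last known to be free". That date comes from the latest trial form received. Section 9.6 uses it for Kaplan-Meier curves and a Cox model.

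**The concern.** Take two participants who both withdraw at month 11. One had a bleed recorded at month 3 and counts as an event. The other had no bleed in 11 months and is removed from the complete-case analysis, or is imputed a bleed with a full year's probability although only one month is unobserved. In scenario one, bleeds among leavers stay in the numerator while bleed-free leavers drop out of the denominator. In scenario three, months of known bleed-free follow-up carry no weight, and a participant who died bleed-free can be imputed a bleed.

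The purpose of this bullet in 9.10 is to show how far missing responses might bias the result. If leaving differs between arms, which is plausible in an open-label comparison of a tablet with repeated endoscopy, the primary coding pulls the risk down in the arm with more leavers and these two scenarios push it up. A reader could take that mechanical disagreement for a real effect of missing data.

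**Working it through.** **Inputs from SAP 4.7.** Risks "from 12% to 8%, a 4% absolute difference"; "2-sided test for comparison of proportions with a 1:1 allocation ratio"; "90% power and a type I error rate of 5"%; "10% attrition/loss to follow-up rate".

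**The plan's own figure.** With pooled variance and no continuity correction, n per group = [1.960·√(2·0.10·0.90) + 1.282·√(0.12·0.88 + 0.08·0.92)]² / 0.04², which rounds up to 1181, or 2362 in total. The SAP states that the design "requires 2362 participants (1181 per group"), so this reproduces. Dividing 2362 by 0.9 gives 2625 against the stated 2630, a small difference that is not at issue here.

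**Assumptions not in the SAP.** Constant hazards of bleeding and leaving, leaving unrelated to bleeding, and attrition varied from 5% to 20% around the SAP's 10%.

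**Complete case.** Let p be the 1-year risk and d the 1-year probability of leaving, with λ = −ln(1−p) and μ = −ln(1−d).

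- Bleed observed before leaving: B = λ/(λ+μ) · [1 − (1−p)(1−d)]
- Bleed-free and still in at one year: S = (1−p)(1−d)
- Set to missing: M = 1 − B − S
- Complete-case risk = B/(B+S); primary-coding risk = B

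For p = 0.12 and d = 0.10: λ = 0.1278, μ = 0.1054, S = 0.88 × 0.90 = 0.792, B = 0.548 × 0.208 = 0.1140 and M = 0.0940. The complete-case risk is 0.1140/0.9060 = **12.6%**. The primary coding gives 11.4%.

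| Attrition, both arms | Complete case (true 12% / 8%) | Primary coding | Complete-case risk ratio (true 0.667) |
|---|---|---|---|
| 5% | 12.3% / 8.2% | 11.7% / 7.8% | 0.667 |
| 10% | 12.6% / 8.4% | 11.4% / 7.6% | 0.668 |
| 15% | 12.9% / 8.6% | 11.1% / 7.4% | 0.669 |
| 20% | 13.3% / 8.9% | 10.8% / 7.2% | 0.669 |

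If all bleeding came before any leaving, 10% attrition would give 0.12/(0.12 + 0.792) = 13.2% in the 12% arm and 8.8% in the 8% arm.

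**Multiple imputation.** A model without follow-up time gives the missing group the complete-case risk: 0.1140 + 0.0940 × 0.1258 = 12.6%, the same as complete case. Under the assumptions, the risk left to these people is (0.1200 − 0.1140)/0.0940 = 6.4%, about half of what is imputed. A simulation of 400,000 participants per arm, with logistic imputation on a baseline covariate, agreed (12.6% / 8.4%). If leaver status entered the model, every observed leaver would be a bleeder and the imputed risk would rise to about 21% / 17%.

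**Unequal leaving (assumed 15% versus 5%).**

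- No true difference, 12% in both arms: complete case 0.1292/0.1228 = 1.05; primary coding 0.1109/0.1170 = 0.95.
- True ratio 0.667, more leaving in the 8% arm: complete case 0.703; primary coding 0.0739/0.1170 = 0.632.
- True ratio 0.667, more leaving in the 12% arm: complete case 0.634; primary coding 0.0780/0.1109 = 0.703.

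**Robustness of direction.**

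- If a leaver's bleed counts only when a 6-month form recorded it before exit, the complete-case risk is 12.3% / 8.2%, still upward.
- The direction reverses if leavers bleed, unreported, at about 2.1 times the usual hazard after exit (2.03 to 2.16 for 5% to 20% attrition).
- If all leaving is bleed-free death, the true 1-year risk at 10% is 11.4%. The primary coding gives exactly that and complete case gives 12.6%.

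**The case against.** A reader might infer that the rule defining who is missing is itself wrong. The SAP does not support that. A recorded bleed settles a yes/no outcome, whereas a participant who exits bleed-free has an unknown status at day 365. Setting leavers who bled to missing would discard observed primary events. The weakness lies in what is done next: dropping the unknowns, or imputing them without time at risk.

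A reader might also infer that every leaver who bled is kept and that the bias is always upward. Neither is assured. The rule turns on a reported bleed, bleeds are identified from the 6- and 12-month forms, and the direction depends on leavers not bleeding unreported at about twice the usual hazard.

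Nor does it follow that the primary analysis fails too. For bleed-free deaths its coding is already correct when death is a competing event. Under the assumptions above, the primary and complete-case figures also bracket the 12%, and some divergence is what a sensitivity analysis is meant to show.

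The effect is small at the SAP's attrition, which section 4.7 calls conservative, and it nearly cancels in the risk ratio. No section of the SAP supports a particular imbalance in leaving.

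Finally, sections 9.4 and 9.6 already use bleed-free time in a Kaplan-Meier and Cox analysis of the same event. This stands in part only: that analysis yields curves and a hazard ratio, not the day-365 risk ratio and risk difference reported for the primary outcome.

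**Conclusion.** The point holds as a modest defect in two of the three missing-data scenarios. Neither the complete-case nor the imputation scenario is specified to use known bleed-free time, and both pool bleed-free deaths with losses. The second scenario only repeats the primary assumption. If leaving is unrelated to later unreported bleeding and the hazard is constant, the overstatement at 10% attrition is about 0.6 points in a 12% arm and 0.4 points in an 8% arm. The risk ratio is practically unchanged with equal attrition. It moves by about 5% with 15% versus 5% leaving, against the direction of the primary coding; that imbalance is assumed. The imputation result further assumes a model without follow-up time, since the SAP specifies none. The primary analysis and the sample size are not affected.

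**What to change.** In 9.10, replace or supplement the complete-case scenario with the day-365 cumulative incidence of first variceal bleed by arm:

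- Censor withdrawn and lost participants at the date last known bleed-free, as derived in 9.4.
- Treat a recorded bleed-free death as a competing event, that is, no bleed, as in the primary coding.
- Report the day-365 risk ratio and risk difference by any standard method, for example pseudo-value regression with the 9.1 covariates.

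If multiple imputation is kept, restrict it to withdrawn or lost participants, impute only over the time remaining after the last known bleed-free date, and impute no bleed after a recorded death. State the imputation model.

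The cost is a change of SAP wording and a little more programming, with no new data. One limit remains: the 9.4 date is that of the last form received, so usable bleed-free time may be shorter than actual time in the trial.

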### 9.3. Handling missing data

In the first instance, analysis will be completed on received data only with every effort made to follow-up participants even after protocol violation to minimise any potential for bias. For the primary outcome, a participant will be assumed to not have experienced variceal bleeding unless there is evidence to suggest otherwise. Therefore, there will be no missing data in this outcome for the primary analysis. However, sensitivity analysis will be performed on the primary outcome measure. See section 9.10 for further details.

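### Of the three missing-data scenarios in SAP section 9.10, one repeats the primary analysis, none lets risk among the missing differ from that of similar observed participants, and active non-returners and deaths are poorly handled

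*SAP*

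**What the plan says.** **Primary rule.** Section 9.3 states that "a participant will be assumed to not have experienced variceal bleeding unless there is evidence to suggest otherwise" and concludes that "there will be no missing data in this outcome for the primary analysis". Section 9.10 restates the rule: "all those recruited who have not reported variceal bleeding within 12 months are assumed to not have experienced the event". Section 9.4 derives the outcome from the 6-month and 12-month follow-up forms.

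**Who becomes missing.** In section 9.10, participants with no reported bleed who "have withdrawn, are lost to follow-up or have died within the 12-month follow-up period are missing the primary outcome response". Those still active at 12 months who "do not return the 12-month follow-up form will not be assumed missing".

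**The three scenarios.** The first is restricted to non-missing responses. The second is "Secondly, it is assumed that those with a missing response did not have variceal bleeding", on the ground that the trial team would learn of a serious bleed through an SAE form. The third is multiple imputation under MAR. All three use the section 9.5 model.

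**The concern.** The stated purpose is to assess the risk of bias from missing responses. Four features weaken that.

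1. The second scenario assumes what the primary analysis assumes, so its agreement with the primary result carries no information.
2. Complete-case analysis and MAR imputation both suppose that missing participants bleed like comparable observed ones. The trial is open-label. Banding participants have repeated endoscopies and carvedilol participants have no routine endoscopic surveillance (sections 4.1 and 4.2). Unseen bleeding that differs by arm is therefore a plausible bias, and no scenario examines it.
3. Without the 12-month form, a bleed in the second half of the year has no stated route into the outcome under section 9.4. Active participants in that position nevertheless stay non-bleeders in all three scenarios.
4. All deaths without a recorded bleed are set to missing, even where bleed status up to death is known. Nothing stops the imputation from assigning a full-year outcome to someone who died early, so missing data and a competing event are mixed.

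**Working it through.** **Coding of each class of participant (sections 9.3, 9.4 and 9.10)**

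| Class | Primary | Complete case | Second scenario | MAR imputation |
|---|---|---|---|---|
| Bleed recorded within 365 days | yes | yes | yes | yes |
| Active, 12-month form returned, no bleed | no | no | no | no |
| Active, 12-month form not returned, no bleed recorded | no | no | no | no |
| Withdrawn or lost, no bleed recorded | no | dropped | no | imputed |
| Died within 12 months, no bleed recorded | no | dropped | no | imputed |

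The primary and second-scenario columns match in every row and the model is the same, so the results must be identical. Row three never changes.

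**How the SAP treats the same gap elsewhere (section 9.4).** Time to first bleed is censored at the completion date of the latest form received. One-year mortality is set to missing when follow-up ends by day 365 and the 12-month form was not returned in its window, although deaths are identified on SAE forms.

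**The plan's own figure (section 4.7).** Inputs: 12% versus 8%, two-sided 5%, 90% power, 1:1.

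n per group = [1.96 × √(2 × 0.10 × 0.90) + 1.2816 × √(0.12 × 0.88 + 0.08 × 0.92)]² / 0.04², which rounds up to 1181, or 2362 in total, as stated. Then 2362 / 0.9 = 2624.4, against 2630 stated (1315 per group), a small rounding up.

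**Illustration.** Assumptions: 1315 per group, unadjusted carvedilol/banding risk ratio (RR), and 95% limits RR × exp(±1.96 × SE), with SE = √(1/e₁ − 1/n₁ + 1/e₂ − 1/n₂), where e is bleeds, n participants, 1 banding and 2 carvedilol. Missingness is set at the planned attrition, 10% of 1315, or about 131 per arm.

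*Rates of 12% and 8% among those with known outcome (1184 per arm; 142 and 95 bleeds):*
- Primary analysis: RR 0.669 (0.522 to 0.858).
- Second scenario: 0.669 (0.522 to 0.858), identical.
- Complete case: 0.669 (0.523 to 0.856). The risk difference moves from −3.6 to −4.0 points.

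*Unequal missingness, primary then complete case:*
- 5% banding, 15% carvedilol: 0.593 (0.462 to 0.763), then 0.663 (0.516 to 0.851).
- 15% banding, 5% carvedilol: 0.746 (0.583 to 0.956), then 0.668 (0.522 to 0.854).

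So departures of the MAR type are tested and can matter.

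*Departure that no scenario examines (10% missing per arm):*
- Missing banding participants bleed at 12% (142 + 131 × 0.12 = 157.7 bleeds). With missing carvedilol participants at 16%, twice the observed rate, carvedilol bleeds are 95 + 131 × 0.16 = 116.0 and RR is 0.735 (0.586 to 0.923). At 24% they are 95 + 131 × 0.24 = 126.4 and the upper limit reaches 1.00.
- No unseen banding bleeds, and recorded bleeding of 12% and 8% of all 1315 (158 and 105 bleeds). With 21 unseen carvedilol bleeds the upper limit is 0.995; with 22 it is 1.002. Starting instead from 142 and 95, the count is 18 (upper limit 1.007).
- The 24% rate falls to about 19.5% with 5% banding and 15% carvedilol missing, and rises to about 40% with the proportions reversed.

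**The case against.** The strongest defence is that two of the three scenarios do real work. A reader might infer that section 9.10 cannot test the primary assumption at all. It can: complete case and imputation replace it for withdrawn, lost and dead participants, and the risk ratio moves when missingness differs by arm. MAR imputation that includes treatment arm would also give missing participants their own arm's rate. What stays untested is narrower: risk among the missing that differs from that of similar observed participants.

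A reader might also infer that active non-returners count as bleed-free throughout the SAP. They do not, because the secondary time-to-first-bleed analysis censors them at their latest form. That analysis still assumes non-informative censoring and is not a sensitivity analysis of the primary risk ratio.

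The SAP argues that a bleed is serious enough to be reported anyway. That is plausible, but the section 9.4 derivation names only the two follow-up forms. The section 9.3 wording about evidence is looser, and the two need to agree.

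It is tempting to say that every death without a recorded bleed has a known outcome. The SAP does not support this: someone who dies before a follow-up form is completed has the same gap as a non-returner, and setting such a death to missing is defensible. Nor does the SAP say that the dead are imputed as if alive. The defect is the absence of any rule.

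A handful of unseen bleeds overturns only a near-threshold result. For example, 149 versus 115 bleeds (z = 2.21) loses significance with 4 more in the carvedilol arm (149 versus 119, z = 1.93). That is not the design case. Finally, the redundancy is not hidden, since both assumptions stand in the same bullet.

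**Conclusion.** The point holds in this limited form. The second scenario is redundant by construction; this follows from the text and needs no assumption. Non-return of the 12-month form by active participants is never varied in the primary analysis or its missing-data scenarios. Deaths without a recorded bleed are handled as one class, without regard to what is known up to death. No scenario departs from MAR other than by repeating the primary assumption.

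At the design effect the primary conclusion would be fairly sturdy. It takes about 22 unseen bleeds among 131 missing carvedilol participants (17%) with none in the banding arm, or about 24% bleeding among them against 12% in missing banding participants. These figures assume 10% missing in each arm and unadjusted risk ratios; the SAP gives only an overall attrition of 10% and does not say whether it includes deaths. The practical risk lies with a smaller observed effect or heavier loss in the favoured arm, where the planned scenarios could not show how little is needed to change the conclusion.

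**What to change.** In section 9.10:

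- Replace the second scenario with multiple imputation under arm-specific shifts from MAR (delta adjustment), and report the combinations of shifts at which the conclusion changes. State the imputation model, including treatment arm.
- In the missing-data scenarios, treat active participants as missing when no 12-month form was returned, no bleed is recorded and bleed status to day 365 is unknown. State how forms completed shortly before day 365 count; the mortality derivation in section 9.4 already has such a rule (day 351).
- Keep deaths as no bleed where bleed status is known up to death, and set them to missing only where it is not.
- State in section 9.4 whether a bleed known only from an SAE form counts towards the primary outcome, so that it agrees with section 9.3 and with the rationale in section 9.10.

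The cost is SAP wording and modest extra programming, with no new data. A composite of bleeding or death would answer a different question and is not needed here.
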